### Subgroups analysis

Five subgroups are analyzed, including the aneurysm location subgroup, the aneurysm maximum diameter subgroup, the different antihypertensive regimen subgroup, the aspirin use subgroup and the statin use subgroup. Subgroup analyses are limited to the primary efficacy endpoint and safety endpoint only. In the subgroup analysis, a separate Cox model will be applied for each subgroup.

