#### Step 2: Randomization and intervention

Enrolled UIA patients will be randomized at a ratio of 1:1 to the EBPL group and SBPL group after obtaining informed consent. Dynamic randomization using the minimization method is used as the randomization of subjects to the EBPL or SBPL group. Randomization and enrollment of subjects are made using the online randomization system. Randomization factors are as follows: age at the time of obtaining the informed consent (≥ 60 years or < 60 years), sex (female or male), aneurysm location [Anterior Communicating Artery (Acom)/Anterior Cerebral Artery (ACA), Internal Carotid Artery (ICA), Middle Cerebral Artery (MCA) and Posterior circulation (PC)]. Patients in the EBPL group are required to keep systolic blood pressure at <120 mmHg and those in the SBPL group at 120-140 mmHg.

This study aims to compare the effects of different blood pressure targets rather than specific medications. Therefore, the blood pressure treatment protocol is flexible in terms of the choice and doses of antihypertensive medications, but there should be preferences based on cardiovascular outcome trials results and current guidelines [such as thiazide diuretic, Calcium Channel Blockers (CCBs), Angiotensin-Converting Enzyme Inhibitors (ACEIs), and Angiotensin II Receptor Blockers (ARBs)]. If adopting another dose frequencies is not required (e.g., twice a day), the preference will be choosing long-acting antihypertensive agents, i.e., once per day.

The cardiologists may select among the available study antihypertensive medications for initiation of therapy. Other drugs not supplied by the trial may also be used as the cardiologists determines appropriate. However, all antihypertensive regimens should include one or more drug classes with strong cardiovascular outcome data from large randomized controlled hypertension trials. If three drugs are needed, a thiazide-type diuretic, a RAS blocker (ACEI or ARB, but usually not both), and CCB make a very effective and usually well-tolerated regimen. The decision is left to the investigator as long as the BP goals are achieved.

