Milepost visit: Milepost visits are used to assist in reaching goal SBP. In this trial, milepost visits will be every 6 months throughout follow-up in both the EBPL group and SBPL group (6th month, 12th month, and 18th month). During each milepost visit, patients will be asked to visit the nearest participating hospital, where cardiologists will measure their blood pressure. This measured blood pressure will be recorded as the milepost visit blood pressure. If the SBP exceeds the target value at milepost visit, then an antihypertensive drug from a class different from what is being taken should be added. Once participant has been prescribed five drugs at maximally tolerated doses, if the SBP remains above goal at subsequent milepost visits, it will be permitted to substitute a different class into the regimen instead of adding another drug or increasing the dose of a drug. However, additional (more than 5) drugs may be needed to achieve goal SBP in some participants. Medication adherence will be assessed routinely in the current trial and should be evaluated especially carefully for participants not at goal on 4 or more medications. Strategies to enhance adherence should be applied.

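### Subgroups by antihypertensive regimen, aspirin and statin use are not fixed at baseline, and the only stated method, a separate Cox model per subgroup, does not test whether effects differ

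*Protocol article*

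**What the plan says.** Subgroups analysis names five factors: aneurysm location, maximum diameter, and "the different antihypertensive regimen subgroup, the aspirin use subgroup and the statin use subgroup". It adds "Subgroup analyses are limited to the primary efficacy endpoint and safety endpoint only", and gives the model as "a separate Cox model will be applied for each subgroup". It does not say whether regimen, aspirin use and statin use are taken before randomisation or during follow-up. It mentions no treatment-by-subgroup term.

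Three other statements decide what an on-study regimen would mean:

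- Step 2 (Randomization and intervention) sets the randomised contrast: "Patients in the EBPL group are required to keep systolic blood pressure at <120 mmHg and those in the SBPL group at 120-140 mmHg".
- The same section leaves drugs and doses open: "The decision is left to the investigator as long as the BP goals are achieved".
- Step 3 (Outcome evaluation, milepost visits) says that when systolic pressure exceeds the target, "an antihypertensive drug from a class different from what is being taken should be added".

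The inclusion criteria also count antihypertensive drugs at entry, from 0 up to 4, so a pre-randomisation regimen exists as well.

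**The concern.** There are two separate problems, and they need separate remedies.

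**Time point.** Drugs are chosen and added until the arm's own target is met, and the enhanced arm's target is lower. A patient on two drugs in the enhanced arm will tend to have hypertension that is easier to control than a patient on two drugs in the standard arm. If on-study regimen defines the subgroup, patients on the same regimen are no longer comparable between arms. The introduction itself calls hypertension an independent risk factor for rupture, so a link between severity and outcome is plausible. Aspirin and statin use have the same undefined time point, although no protocol rule ties them to the arm.

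**Method.** Separate models give one estimate per subgroup but no test of whether the estimates differ. Readers then tend to compare which subgroups reached significance, and with smaller subgroups that comparison often shows a difference where none exists.

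At stake are published subgroup statements on the primary efficacy and safety endpoints. The main comparison is not at stake.

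**Working it through.** **1. The plan's own figure.** Inputs from Sample size: control risk 20.7%, halved to 10.35%, α = 0.05 two-sided (the sidedness is given under Endpoint and outcome evaluation), and the stated β = 0.90 read as power.

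n per group = (1.960 + 1.2816)² × (0.207×0.793 + 0.1035×0.8965) / 0.1035² = 10.507 × 0.25694 / 0.010712 = 252.03, rounded up to 253. With 10% dropout, 253/0.9 = 281.1, rounded up to 282. Both match the protocol, so 90% power is a fair starting point.

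**2. Separate models when every patient has the same effect.** At 90% power the expected overall z is 1.960 + 1.2816 = 3.2416.

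- Two equal halves: z = 3.2416/√2 = 2.292, so power in each is Φ(2.292 − 1.960) = 0.63. The chance that exactly one is significant is 2 × 0.63 × 0.37 = 0.47.
- Four equal quarters (Step 2 lists four locations): z = 1.621, so power in each is 0.367. The chance that they are not unanimous is 1 − 0.367⁴ − 0.633⁴ = 0.82.

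The same check by event counts, with 253 per group, a halved risk and variance of log HR = 4/events:

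| Control risk | Events | HR | Overall power | Power per half | Halves disagree |
|---|---|---|---|---|---|
| 20.7% | 253 × (0.207 + 0.1035) = 78.6 | ln(0.8965)/ln(0.793) = 0.471 | 0.92 | 0.655 | 45% |
| 11.5% | 253 × (0.115 + 0.0575) = 43.6 | ln(0.9425)/ln(0.885) = 0.485 | 0.67 | 0.394 | 48% |

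The range is therefore 45% to 48%. The upper end goes with the lower control risk, where overall power is no longer 90%. A valid interaction test at the 5% level would signal in 5% of such trials.

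**3. Splitting on an on-study regimen when there is no effect.** None of the inputs to this part except the 11.5% risk comes from the document. Latent severity is standard normal. Drug count = round(1.8 + shift × enhanced arm + 0.8 × severity + noise). The 11.5% two-year risk is multiplied by an assumed severity HR per SD. The true arm effect is nil, and the overall risk ratio came out at about 1.00 throughout. Each cell gives the range over the two strata (at most 2 drugs, at least 3 drugs):

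| Extra drugs in enhanced arm | Noise SD | Severity HR 1.3 | HR 1.5 | HR 2.0 |
|---|---|---|---|---|
| 1.0 | 0.5 | 0.87 | 0.80–0.81 | 0.68–0.71 |
| 1.0 | 1.0 | 0.92–0.93 | 0.88–0.89 | 0.81–0.83 |
| 0.5 | 1.0 | 0.95–0.97 | 0.93–0.94 | 0.90–0.92 |

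A second set of runs, with its own inputs and a risk of about 16%, gave 0.79 to 0.96. If severity is unrelated to risk, or the target does not change the regimen, the ratio stays at about 1.00.

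The mechanism shows in the strata. With one extra drug and noise SD 1.0, mean severity among patients on at most 2 drugs is about −0.6 in the enhanced arm and −0.3 in the standard arm. Among those on at least 3 drugs it is about 0.4 and 0.7. Both strata are tilted the same way, towards the enhanced arm.

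**The case against.** A reader might infer that the plan does split on a post-randomisation regimen. The text does not go that far. It gives no time point, the inclusion criteria record a drug count at entry, and Table 1 places clinical information at screening with no medication row during follow-up. A baseline reading is natural. What stands is that the section permits both readings, that only one of them is valid, and that the regimen described at length in the protocol is the one titrated after randomisation.

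A reader might also infer that the plan rejects an interaction test. It is silent. The section calls each factor a subgroup, so one model per factor is a possible reading, and such a model could hold a treatment-by-factor term. A full protocol or analysis plan may say so. Still, the article does commit to a method, and the wording as it stands tests no difference in effect. Nor does it say that benefit will be claimed wherever p < 0.05: hazard ratios with confidence intervals are planned. The 47% and 82% figures describe what a reader comparing significance would meet, and they assume equal-sized subgroups. The document gives no location distribution.

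A third tempting claim is that splitting by regimen produces false differences between subgroups. In the simulation both strata shift alike, so the harm is bias within each stratum, and an interaction test would neither detect nor cure it. The size of that bias rests on assumptions, and on splitting by drug count; regimen could instead mean class or combination, for which there is no figure.

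**Conclusion.** The point holds as a matter of badly fixed wording. Regimen, aspirin use and statin use are named as subgroup factors without a baseline definition, in a trial whose titration rules make the on-study regimen depend on the arm. If on-study regimen is used, the within-regimen comparison is confounded and can be biased. A true null appearing as a risk ratio of about 0.7 to 0.96 is illustrative only, and the bias vanishes if severity does not affect risk or the target does not change the regimen.

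Separately, one Cox model per subgroup does not test heterogeneity. That conclusion rests on the stated method and on arithmetic from the protocol's own design figures, given equal halves and a common effect. Severity is low: these are subgroup analyses on two endpoints, and the primary analysis is untouched.

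**What to change.** 1. State that the regimen, aspirin and statin subgroups are defined by status before randomisation. For regimen, the number of antihypertensive drugs at entry would serve, since eligibility already requires it. Otherwise drop on-study regimen as a subgroup.
2. For each of the five factors, fit one Cox model on all patients with arm, factor and their interaction. Report the interaction p-value and the subgroup hazard ratios with confidence intervals from that model, labelled exploratory.

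Both steps are needed: the first removes the regimen bias, the second replaces the comparison of separate models. The cost is minor wording and analysis work. The document shows drug count at entry but does not show that baseline drug class, aspirin use and statin use are recorded, so that must be confirmed first.

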### Data management

The clinical research coordinator (CRC) will conduct regular visits to each participating center to ensure the strict implementation of the research program. If there is any conflict with the research program, CRC will be reported to investigators in a timely manner. In addition, throughout this study, a summary meeting will be held every 3 months to discuss and solve any problem arising from the research or encountered by the patients.

All data will be collected and stored using a case report form (CRF), and the completed CRFs will be sent back per 3 months. In addition, the data will be also transcribed into an electronic version by nine investigators independently. After completion, the CRFs will be sealed in a research-specific cabinet and electronic data will be stored by a specific person. A data management committee was established to supervise data quality and ensure data security. Data is only open to research team members. The privacy of patients is protected.

### Ethical considerations

This study was approved by the Institutional Review Board. The research would be conducted in strict accordance with the declaration of Helsinki and Human Biomedical Research Ethical Issues. All enrolled subjects will be informed with a complete and comprehensive introduction, including the study’s purpose, procedure, potential risks, and potential benefits. The patient’s family should sign the written informed consent before beginning. They will be informed that they have the right to withdraw from the study at any time, and informed consent will be retained as a clinical study document for future reference. The subject’s personal privacy and data confidentiality will be protected during the study.

## Discussion

Hypertension has long been considered a risk factor for aneurysm growth and rupture (1, 11). The ChATIA study is the first clinical trial to investigate the optimal blood pressure management of Chinese UIA patients. In this study, we investigate whether enhanced blood pressure lowering therapy can prevent UIA instability without increasing the risk of ischemic cerebral or cardiac events.

The formation, growth and rupture of the intracranial aneurysm have been proven to have a strong correlation with hypertension. Abnormal hemodynamics and destruction of arterial walls induced by hypertension play a significant part in intracranial aneurysm growth and rupture (18, 19). Previous studies and guidelines recommend effective antihypertensive therapy can reduce the risk of aneurysm instability (17, 20). Notably, intensive blood pressure reduction therapy may increase the risk of ischemic cerebral and cardiac events as reported in several studies (12–14). However, the optimal blood pressure range for UIA patients remains unknown.

The ChATIA trial aims to investigate the optimal blood pressure management strategy for the Chinese UIA population. The efficacy and safety of enhanced antihypertensive therapy will be further verified in this study.

## Conclusion

In summary, we have described a clinical trial for enhanced blood pressure reduction therapy for UIA patients with hypertension. The efficacy and safety of blood pressure reduction will be discussed in this study, which will provide evidence for blood pressure management in the future.
